This confirmatory efficacy R01 trial focuses on two non-pharmacological treatments that each work for some SAD patients: light therapy (LT; i.e., daily exposure to bright artificial light during the symptomatic months), and SAD-tailored group cognitive-behavioral therapy (CBT-SAD) [11]. Substantial evidence supports LT as an efficacious acute SAD treatment [12]. In our previously completed R01-level efficacy trial enrolling 177 adults with SAD, CBT-SAD and LT were very similar in terms of symptom improvement and the proportions in remission at post-treatment (47.6% CBT-SAD, 47.2% LT) [13]. However, two winters later, CBT-SAD was associated with significantly fewer depression recurrences (27.3% CBT-SAD, 45.6% LT) and lower depression severity than LT [14]. These findings suggest that slightly more than one-quarter of those treated with CBT-SAD and slightly less than half of those treated with LT have a depression recurrence, highlighting the need for reliable strategies for precision medicine in clinical practice. In the current project, we apply the experimental therapeutics approach to determine how each treatment works and to identify the best candidates for each. Consistent with the NIMH’s focus on biological endpoints, we will ascertain whether theoretically derived candidate biomarkers of each treatment’s target and effect are prescriptive of better outcomes in that treatment vs. the other.

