#### Targets and biomarkers of CBT-SAD’s response

Consistent with the experimental therapeutics perspective, the proposed work intends to map seasonal beliefs onto biomarkers of CBT-SAD’s target and effect. Evidence supports that CBT for non-seasonal depression works via altering mechanisms of maladaptive thought patterns. Sustained pupil dilation to emotional words, which indexes prefrontal control mechanisms associated with emotion regulation [36, 37], is a potential biological mechanism of CBT response. Sustained frontal gamma-band EEG responses to emotional stimuli indicates sustained elaborative emotional processing and potentially sustained regulatory effort [38], is a biomarker of depression [38], and represents another candidate biomarker of CBT for depression’s target and effect. In SAD, we propose that maladaptive thoughts are dominated by seasonal- and light-related themes, matching the content of seasonal beliefs that appear mechanistic of CBT-SAD. Therefore, we will explore whether pupil dilation and EEG responses to seasonal words change more during CBT-SAD than LT (target engagement) and whether these changes are prescriptive of better outcomes in CBT-SAD than in LT, in the way that seasonal beliefs are. Such findings would indicate that patients who do not recur following CBT-SAD are less emotionally reactive to seasonal stimuli, thereby engaging in less elaborative processing of these stimuli and requiring less prefrontal control to regulate their emotional responses to them.

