### Outcomes {12} (Table 1)

#### Primary outcome: structured interview guide for the Hamilton Rating Scale for Depression—Seasonal Affective Disorder Version (SIGH-SAD

The SIGH-SAD (42) includes the 21-item Structured Interview Guide for the Hamilton Rating Scale for Depression (HAM-D) and a supplementary 8-item subscale to assess atypical depressive symptoms associated with SAD. A trained rater, blind to treatment condition, will administer the SIGH-SAD at pre-treatment, treatment weeks 1–5, post-treatment, and winter follow-ups. The rater will always begin by asking if any new treatment other than the study treatment has been initiated and if any medications have changed. This will be coded in the database and considered as a possible covariate. A second blinded rater will rate audio-recordings of the SIGH-SADs to assess inter-rater reliability. The depression recurrence (primary outcome) criteria define SAD episode onset or recurrence [62] and were used in our prior trials: total SIGH-SAD score ≥ 20 + HAM-D score ≥ 10 + atypical score ≥ 5. Remission at treatment endpoint is classified by satisfying one or both of the following criteria [62]: (1) pre- to post-treatment reduction in total SIGH-SAD score ≥ 50% + HAM-D score ≤ 7 + atypical score ≤ 7, OR (2) HAM-D score ≤ 2 + atypical score ≤ 10. The same criteria will be applied to winter follow-up remission status by comparing follow-up to pre-treatment scores. We will follow our published SIGH-SAD protocol for item scoring rules, rater training procedures, and resolving rater discrepancies [63]. SIGH-SADs were administered live until March 2020 when we shifted to HIPPA-compliant videoconference due to the COVID-19 pandemic.

**Table 1 Tab1:** Measures and assessment schedule

Measure	Construct assessed	Metric	Pre-TX	Weekly during TX	Mid-TX*	Post-TX*	Winter 2	Winter 3
SIGH-SAD [42] (see description)	SAD recurrence (primary outcome) and remission status, symptom severity	Categorical recurrence status, categorical remission status, score	X	X	X	X	X	X
Beck Depression Inventory-II (BDI-II) [52]	Depression symptom severity, remission status (BDI-II ≤ 8)	Score, categorical remission status	X	X	X	X	X	X
Beck Anxiety Inventory [53]	Anxiety symptom severity	Score	X		X	X	X	X
Dim light melatonin onset (DLMO)	Circadian timing	Clock time (military)	X			X	X	X
Wrist actigraphy and Pittsburgh Sleep Diary [54]	Sleep & circadian timing; daytime activity	Mean mid-point of sleep; mean daily activity count	X			X	X	X

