### Sample size {14}

With a target *N* = 160 (80 subjects in each of the two treatments), the study will have 80% power to detect main effect differences of 22% (e.g., 28% vs. 50%) in winter 2 recurrence, which we expect at a naturalistic follow-up [14, 44]. Sample sizes for comparisons of winter 3 recurrence will depend on the number of recurrences at winter 2. Based on the recurrence rates observed in our prior study, we project that there will be about 37 recurrences in the LT group and 22 recurrences in the CBT-SAD group. This will provide 80% power to detect a difference in winter 3 recurrence of 35% (e.g., 60% vs. 25%) between CBT-SAD➔LT and LT➔CBT-SAD and a difference of 27% (e.g., 23% vs. 50%) between CBT-SAD and LT subjects without winter 2 recurrence. For biomarker comparisons, there will be 80% power to detect differences of 0.45 standard deviation (SD) in post-treatment values or in pre-post treatment changes between CBT-SAD and LT. Power for detecting relationships between biomarkers and outcomes were based on the odds ratio associated with an increase of 1 SD in the biomarker value or its change. For post-treatment remission, there will be 80% power to detect an OR of 2.2 in the CBT-SAD or LT group and a 2.4-fold difference in the ORs for the two treatments. For winter 2 recurrence, there will be 80% power to detect an OR of 2.2 in the LT group, an OR of 2.8 in the CBT-SAD group, and a 2.9-fold difference in their ORs. There was minimal attrition (4.5%) in our previous study, and we anticipate similar retention in this study. However, with attrition as high as 20%, there will be 80% power to detect a difference in winter 2 recurrence of 24% between CBT-SAD and LT and a difference of 39% in winter 3 recurrence between the two switch groups. Empirical sample size estimates^21^ indicate that the study will have at least 80% power to detect a mediated effect if the regression coefficient for the direct effect of treatment after adjustment for the mediator is at least .39 and the coefficients for the effect of treatment on the mediator and the effect of the mediator on outcome after adjustment for treatment are at least .26.

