To examine mechanistic differences between CBT-SAD and LT, mixed effects linear regression with subject as a random effect will be used to model biomarker changes during treatment as a function of time, treatment, and their interaction. We will also model the relationship between biomarker change and change depressive symptoms as a function of treatment by letting the regression coefficient differ between CBT-SAD and LT. This will provide a test of whether potential mediators of effect are treatment-specific. The predictive value of biomarkers at baseline, their pre-post treatment change, and the persistence of the change at follow-up will be examined using logistic regression (for post-treatment remission and winter 2 recurrence) and linear regression (for SIGH-SAD and BDI-II scores) with post-treatment and winter 2 outcomes as dependent variables. Interactions between the biomarkers and treatment will be used to test if the associations with outcomes differ in the CBT-SAD and LT groups. Adherence will be included in ancillary analyses to test its effect on the relationships of treatment with biomarkers and LT or CBT-SAD outcomes. The relationships between biomarkers and outcomes will be validated by examining how well they predict post-treatment and winter 3 outcomes for subjects who experience a recurrence at winter 2 and are switched to the alternative treatment. Data from the cross-over subjects will also be analyzed using mixed linear regression to compare within-person differences in pre-treatment biomarkers and their changes during their initial and subsequent treatments. Treatment, time point (winter 1 or 2), and their interaction will be included to test the effect of treatment sequence on within-person differences in biomarker responses to CBT-SAD and LT.

##### Aim 3

Logistic and linear regressions similar to those for Aim 1 will be used to compare the effect of switching from CBT-SAD➔LT versus LT➔CBT-SAD on winter 3 recurrence and depression scores. Post hoc adjustment for any differences between switch groups in baseline characteristics, treatment response, and biomarker profiles will be done by including them as covariates. Mixed linear regression will be used to longitudinally model depression scores over the three winters, with treatment as a time-varying covariate.

##### Aim 4

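### The Aim 2 models relating biomarkers to depression outcomes do not name the pre-treatment depression score as a covariate, so a marker's main effect can reflect severity at entry

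*Protocol article*

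**What the plan says.** The protocol article, Statistical methods {20a}, Aim 2, examines three biomarker predictors: the baseline value, the change over treatment, and how far that change persists. Logistic regression is used for post-treatment remission and winter 2 recurrence, and "linear regression (for SIGH-SAD and BDI-II scores) with post-treatment and winter 2 outcomes as dependent variables". Biomarker-by-treatment interactions test whether associations differ between arms. Adherence enters in ancillary analyses.

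Covariates are named elsewhere, but none is the entry score:
- wake time, for the post-illumination pupil response (PIPR);
- time of testing and chronotype or melatonin onset, for the word task;
- an open list of examples for secondary analyses (section {20b}): sex, age, race, ethnicity, number of prior episodes.

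The background says that sustained frontal gamma "is a biomarker of depression", and that PIPR in winter is lower in people with SAD than in controls. The SIGH-SAD and BDI-II are both scheduled before treatment (Table 1). The first remission criterion is "pre- to post-treatment reduction in total SIGH-SAD score ≥ 50% + HAM-D score ≤ 7 + atypical score ≤ 7"; the alternative criterion uses absolute cut-offs only.

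**The concern.** Randomisation balances the arms. It does not balance people with high and low values of a pupil, EEG or circadian measure. If such a measure tracks how depressed someone is at entry, and entry severity predicts later severity, the measure will be associated with the outcome even if it carries no further information. This is confounding of an observational predictor, and it is separate from the precision of the randomised comparison.

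The stated objective is to learn which patients suit which treatment. Every participant will already have an entry SIGH-SAD and BDI-II, so a laboratory marker helps with that choice to the extent that it adds to those scores. A model without them cannot separate the two contributions.

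**Working it through.** **Inputs from the protocol article.** "With a target *N* = 160 (80 subjects in each of the two treatments"). Biomarker comparison between arms: "there will be 80% power to detect differences of 0.45 standard deviation (SD) in post-treatment values or in pre-post treatment changes". The biomarker–outcome power figures "were based on the odds ratio associated with an increase of 1 SD in the biomarker value or its change". Remission: "For post-treatment remission, there will be 80% power to detect an OR of 2.2 in the CBT-SAD or LT group". Prior-trial remission: "the proportions in remission at post-treatment (47.6% CBT-SAD, 47.2% LT"), mean 47.4%. Entry requires SIGH-SAD ≥ 20.

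**Assumed, because the documents do not give them.** Two-sided 5% tests; marker–severity correlation r = 0.2–0.4; severity–outcome correlation q = 0.3–0.5.

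**Step 1: the plan's own figures.** For 0.45 SD, the standard error is √(2/80) = 0.158. Then 0.45/0.158 − 1.96 = 0.886, and the power is Φ(0.886) = 0.81. For OR 2.2 per SD, the logistic sample-size formula for one normal covariate with the large-effect correction uses b = ln 2.2 = 0.788 and δ = 2.44:

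n = (1.96 + 0.842·e^(−b²/4))²·(1 + 2pδ)/(p·b²) = 7.185 × 3.312/0.2947 ≈ 81, against 80 stated.

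The simpler formula, (1.96 + 0.842)²/[p(1 − p)b²], gives 51. The stated figures are therefore reproduced or conservative, and none is disputed. Both calculations use the biomarker alone.

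**Step 2: main effect on the score.** Let severity S drive both the marker (r) and the outcome (q), with no direct link between marker and outcome. The induced correlation is r·q. With N = 160 the expected z is √157·atanh(rq), and the rejection rate is P(Z > 1.96 − z) + P(Z < −1.96 − z).

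| r | q | rq | z | significant without S |
|---|---|---|---|---|
| 0 | any | 0 | 0 | 5% |
| 0.2 | 0.3 | 0.06 | 0.75 | 12% |
| 0.3 | 0.4 | 0.12 | 1.51 | 33% |
| 0.4 | 0.5 | 0.20 | 2.54 | 72% |

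Simulation over the same range gave roughly 13–69%, in line with the formula. With S in the model the rate is about 5% throughout. At r = 0.1 (q = 0.2–0.5) the unadjusted rate is only 6–10%.

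**Step 3: remission.** HAM-D ≤ 7 plus atypical ≤ 7 caps the total at 14. The 50% rule demands a lower total than 14 whenever the entry score is below 28, that is, for entry scores of 20 to 27. Milder entrants must therefore reach a lower score, which partly offsets the confounding. With that rule modelled, simulation gave roughly 6–31% unadjusted.

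**Step 4: biomarker-by-treatment interaction.** If severity acts alike in both arms, the unadjusted test stays at about 5%. If it acts in one arm only, the marker slopes differ by rq. At r = 0.4, q = 0.5 the standard error is √[(0.75 + 0.96)/80] = 0.146, so z = 0.20/0.146 = 1.37 and the rate is about 28%. At r = 0.2, q = 0.3 it is about 7%. Simulation gave roughly 7–21%, so the upper end is approximate. Adding S as a main effect does not repair this (5–41% over r = 0.1–0.5, against 5–40% without it). Adding S × treatment does (about 4–6%).

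**Not covered.** These figures concern a single marker value. For the change and persistence predictors the same mechanism applies only so far as they correlate with entry severity, and its size was not worked out.

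**The case against.** The strongest reply is that silence is not exclusion. This is a condensed article, and the analysis plan, which is not shown, may list the covariates. A reader might infer that Aim 2 rules out baseline severity, or that the power figures prove an unadjusted model because they reproduce with the biomarker alone. The documents support neither: the text never calls the models unadjusted, and a single-predictor power calculation does not fix the analysis model. What stands is that the article lists the terms of these regressions and names covariates for other analyses. Under Aim 3 it also plans post hoc adjustment for differences in baseline characteristics between the switch groups, which are not randomised either. The entry score is never among the Aim 2 terms.

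A reader might also infer that state-related markers will be declared predictive. That needs a marker–severity correlation among people who have all passed the entry threshold. A contrast between patients and controls does not supply it, and the threshold narrows the range of severity.

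The test most relevant to treatment matching is the interaction, which holds unless severity acts differently by arm. That possibility is not remote: Aim 1 imputes separately by arm because, in the prior trial, some imputation predictors related to recurrence differently in the two treatments. Baseline SIGH-SAD is among those predictors, though it is not singled out.

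Three further points stand. An unadjusted association is a legitimate crude prediction. Entry severity already enters the Aim 2 change-on-change model and the Aim 4 latent intercepts, although these are different analyses. For PIPR, the background proposes that retinal subsensitivity lies upstream of SAD, so adjusting for severity could remove part of a real association.

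**Conclusion.** The point holds as a correctable weakness in the models as described, not as a demonstrated error. No stated figure is wrong and no sections contradict each other. The Aim 2 outcome regressions do not name the pre-treatment score, and without it a main effect cannot support a claim that a biomarker adds to entry severity.

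Under the assumed correlations, a marker with nothing to add is significant in roughly 13–69% of trials for the score and 6–31% for remission. For the score, adjustment brings this to about 5%. If the marker is unrelated to entry severity there is no inflation. The interaction test is at risk only when severity acts differently by arm. The calculation also assumes that severity drives the marker; if the marker is upstream, the unadjusted association is partly genuine.

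**What to change.** Add the pre-treatment value of the outcome scale to the Aim 2 outcome regressions: SIGH-SAD for SIGH-SAD scores, remission and recurrence; BDI-II for BDI-II scores. Where a biomarker-by-treatment interaction is tested, also add the product of that score with treatment. Base any claim that a biomarker adds to baseline severity on the adjusted estimate, and show the unadjusted association beside it, so that possible over-adjustment for an upstream marker is visible.

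The data are already scheduled. The cost is one or two degrees of freedom and some power for the biomarker term when it correlates with severity. Required n rises by about 1/(1 − r²): for OR 2.2 and remission, 81 becomes 81/0.91 = 89 at r = 0.3 and 81/0.75 = 108 at r = 0.5, against 80 per arm. On the simpler formula the detectable OR at n = 80 moves only from 1.87 to 1.93 and 2.06, still below 2.2. For the score models there is a partial return: adjustment removes q², or 9–25%, of the outcome variance at q = 0.3–0.5.

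### The check of biomarker–outcome relationships in winter 2 switchers is called validation, but the group is nested in the fitting cohort, selected on recurrence and too small to support that word

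*Protocol article*

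**What the plan says.** Under Statistical methods {20a}, Aim 2, biomarkers at baseline, their change during treatment and the persistence of that change enter logistic and linear regressions "with post-treatment and winter 2 outcomes as dependent variables". Treatment-specific associations are allowed for: "Interactions between the biomarkers and treatment will be used to test if the associations with outcomes differ in the CBT-SAD and LT groups".

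The plan then states: "The relationships between biomarkers and outcomes will be validated by examining how well they predict post-treatment and winter 3 outcomes for subjects". The group meant is restricted to participants "who experience a recurrence at winter 2 and are switched to the alternative treatment". It does not say whether pooled or treatment-specific coefficients are carried into that check, or to which switchers they are applied.

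On numbers, Sample size {14} has "With a target *N* = 160 (80 subjects in each of the two treatments" and projects "about 37 recurrences in the LT group and 22 recurrences in the CBT-SAD group". Trial design {8} makes cross-over an offer, so not everyone who recurs need switch. The same sample size section gives detectable odds ratios for biomarkers in the full arms, but no power for the check in switchers.

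**The concern.** Objectives {7} sets out to find which patients suit which treatment. A biomarker reported as validated for that purpose is one a clinician might act on. The word implies that a relationship found in one set of patients was confirmed in another set that represents the intended users. Three features of the switcher group stand in the way.

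- **Nesting.** Every switcher was randomised and so belongs to the cohort used for fitting.
- **Selection.** Every switcher recurred at winter 2, which is one of the modelled outcomes, and did so after a first treatment. Range restriction and carry-over from that treatment could move an association either way, and performance in this group need not transfer to patients choosing a first treatment.
- **Size.** Each treatment's relationship can be checked only in the few people switched to it.

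A chance relationship could be called validated, and a true one could appear to fail.

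**Working it through.** **1. Size of the checking group.** Background {6a} gives the prior rates: "CBT-SAD was associated with significantly fewer depression recurrences (27.3% CBT-SAD, 45.6% LT". With 80 per arm, 80 × 0.456 = 36.5 and 80 × 0.273 = 21.8. This reproduces the projected 37 and 22. Together they make 59, or 59/160 = 37% of the fitting sample. Refusals lower this, so 59 is a ceiling under the projected rates. The LT relationship is checked in at most about 22 people (CBT-SAD to LT) and the CBT-SAD relationship in at most about 37 (LT to CBT-SAD).

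**2. The plan's own detectable effect.** Sample size {14} states 80% power for an odds ratio of 2.2 per SD on post-treatment remission within one arm. Inputs: n = 80, remission about 0.474 (prior trial 47.6% and 47.2%), two-sided 5% (assumed, since the article gives no alpha here). The Hsieh 1989 logistic formula returns a detectable odds ratio of 2.23, which matches. Simulated likelihood-ratio tests give about 90% power at n = 80, so the stated figure is somewhat conservative.

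**3. Power for the same effect in switchers.** Large-sample formula: power = Φ(ln 2.2 × √(n × p(1 − p)) − 1.96), with ln 2.2 = 0.788 and p(1 − p) = 0.474 × 0.526 = 0.249.

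| n | Calculation | Formula | Simulation |
|---|---|---|---|
| 80 | Φ(0.788 × 4.46 − 1.96) = Φ(1.56) | 94% | 90% |
| 37 | Φ(0.788 × 3.04 − 1.96) = Φ(0.43) | 67% | 61% |
| 22 | Φ(0.788 × 2.34 − 1.96) = Φ(−0.11) | 45% | 39% |

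The simulation is the better guide at these sizes. If winter 3 recurrence in switchers followed the prior winter 2 rates, simulated power would be 40% for an odds ratio of 2.2 at n = 22 (rate 45.6%). It would be 71% for the plan's larger odds ratio of 2.8 at n = 37 (rate 27.3%).

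**4. False confirmation with no true effect.** Simulation: 80 per arm, no biomarker–outcome association, continuous biomarker and outcome each correlated within person across winters, and switchers taken as the 37 (LT) and 22 (CBT-SAD) with the highest winter 2 scores. There were 20,000 replicates per setting, of which about 1,000 had a significant winter 1 association. Confirmed means same sign and two-sided p < 0.05 in switchers, so the nominal rate is 2.5%. The correlations are assumptions; the article gives none.

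| Cross-winter correlation (biomarker, outcome) | Pooled slope: fitted in 160, checked in 59 | CBT-SAD slope: fitted in CBT-SAD arm, checked in 37 LT-arm switchers |
|---|---|---|
| 0, 0 | 2.2% | 2.7% |
| 0.5, 0.3 | 3.1% | 2.2% |
| 0.7, 0.5 | 5.2% | 2.4% |
| 0.9, 0.7 | 9.1% | 1.8% |

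With about 1,000 conditional replicates, the simulation standard error is roughly 0.5 points at 2.2% (√(0.022 × 0.978/993)) and 0.9 points at 9.1% (√(0.091 × 0.909/998)). Variants of the pooled set-up under other assumptions gave 4–7% and 2.6–3.6%; a further opposite-arm run gave 2.4–3.2%. Inflation is therefore confined to pooled slopes and depends on how strongly people resemble themselves from winter to winter.

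**The case against.** A reader might infer that the check is circular, because relationships are tested in the same people who produced them. The documents do not support that in general. The outcomes to be predicted, after the switch and at winter 3, are new. Under Plans for assessment and collection of outcomes {18a}, biomarkers are measured again at winter 2 and during the second treatment. With a biomarker-by-treatment interaction, the LT slope comes from the LT arm and would be checked in CBT-SAD-arm patients switched to LT, and the reverse for CBT-SAD. Those are different people, and the opposite-arm column above shows no inflation. This part of the objection stands. The overlap problem is limited to whatever is pooled across arms, and it arises at all because the article does not say which coefficients are used.

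It can also be said that the plan sets no significance threshold in switchers, only that prediction will be examined, and that linear models of SIGH-SAD and BDI-II scores are planned as well. That is fair. The power figures apply to binary outcomes and serve as a gauge of how little 22 or 37 people can settle.

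Finally, resampling methods are often left to a statistical analysis plan, and they reuse the same cohort. Their absence from the article is not the point here. The point is that the article names a validation step that cannot carry the name. Resampling is no external test either, but it corrects optimism in the population of interest, which is patients starting a first treatment.

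**Conclusion.** The concern holds in a limited form. The switcher analysis is a useful check in the opposite arm and in a later winter, but it is not validation.

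- For slopes pooled across arms, overlap raises false confirmation above 2.5%, to about 5–9% under strong assumed cross-winter correlations and less under weaker ones.
- For treatment-specific slopes checked in the opposite arm there is no such inflation. The group is still selected for recurrence after a first treatment, and power for an odds ratio of 2.2 is about 40% (n = 22) and 60% (n = 37), assuming remission near 47% and a two-sided 5% test.

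Neither agreement nor failure in switchers would settle whether a biomarker predicts outcome in first-line patients. The documents do not support going further and calling the check circular, or dropping it. The consequence is confined to what Aim 2 may claim about prescriptive biomarkers; the Aim 1 comparison of recurrence is untouched.

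**What to change.** Make three changes to Aim 2.

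1. Estimate the predictive performance of the biomarker-by-treatment models in the full randomised sample, using an optimism-corrected bootstrap or repeated cross-validation that repeats every model-building step.
2. Keep the switcher analysis and state its rule: the LT coefficients estimated in the LT arm are applied to CBT-SAD-to-LT switchers, and the CBT-SAD coefficients estimated in the CBT-SAD arm to LT-to-CBT-SAD switchers. Report it with confidence intervals.
3. Describe that analysis as exploratory, and reserve the word validation for an independent sample.

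The cost is analysis code and wording, with no new data. The downside is small: somewhat more work, and corrected performance that will look less favourable than the apparent performance.
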